### Participant recruitment

It is estimated that around 300 patients per practice (based on an average practice size) will undertake the pre-screening over a 12 month period, which will result in approximately a total of 12 000 patients completing the pre-screen survey. Out of these 12 000, we expect dyspnoea rates of around 10%. However, considering variations in severity/duration of breathlessness and patient consent means we are allowing for 3/4 patients not to proceed to the CDSS, resulting in a total of 400 (200 per arm) who will be identified as having chronic dyspnoea and who will consent to the BREATHE study. This means a target for each practice to recruit a minimum of 10 participants, who will be followed up for 12 months.

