### Trial design

The pragmatic implementation trial will be a cluster randomised controlled 2-arm trial (RCT) in 40 primary care sites. Each arm will comprise 20 practices, outlined below:

ARM 1: pre-screening for chronic dyspnoea and standard of care management.

ARM 2: pre-screening for chronic dyspnoea and CDSS guided management

Practices will be recruited from urban, regional and rural areas and individual GPs within each practice will consent to participate. Recruitment of patients will continue for 12 months. We will purposefully sample practices from all categories to ensure representation of each region (metropolitan, regional, rural) is equal in each arm. The randomised ‘units’ in this cluster RCT are the GP practices. The GP practices will be enrolled over time, so the randomisation list will be created by an unblinded statistician and (blinded to the study team) include a schedule within each regionality using randomly permuted blocks (a mix of size two or four) to ensure balance, and we will allocate and advise the study team as sites are activated, as GP practice allocation will be unblinded to both the study team and the GP practice.

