### Statistical analyses

The primary outcome is change in D-12 score, which has a minimum clinically important difference of 2.83 (out of a possible score of 36).^37^ Assuming a two-arm parallel cluster trial with a baseline measure, a total of 40 GP practices (clusters) provides 90% power to detect a mean difference in D-12 of four points at 0.05 significance level. To achieve this, each practice will be expected to recruit a minimum of nine participants who will be followed up for 12 months each. Allowing for a drop-out rate of 10%, we aim to recruit 10 participants per cluster for a total of 400 participants. A conservative SD of D-12 of 15 points and individual autocorrelation (the correlation between observations from the same individual at different times) of 0.65 is assumed. These calculations are robust to values of the intra-cluster correlation coefficient up to 0.10.

The primary analysis will compare change in D-12 scores at 12 months between the CDSS and standard care arms. The analysis will be performed using a repeated-measure linear mixed model including measurements taken at baseline, 3, 6 and 12 months. The model will include the effect of the visit, the randomised group and the interaction between randomised group and visit. A random cluster effect will be used to model within-cluster correlation, and a repeated effect will be used to model within-patient correlations.

A similar approach will be used to analyse secondary outcomes with logistic regression used in place of linear regression for binary outcomes. Controlled multiple imputations^38^ will be used to assess the robustness of the primary outcome results to different missing data assumptions. Sensitivity analyses including additional covariate adjustments will also be performed. A detailed statistical analysis plan will be developed and made publicly available before any analysis.

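### The stated screening rates yield 300 participants, not the 400 (200 per arm) that the recruitment section says they produce

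*Protocol article*

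**What the plan says.** Trial design describes a "cluster randomised controlled 2-arm trial (RCT) in 40 primary care sites. Each arm will comprise 20 practices", with patient recruitment lasting 12 months.

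Participant recruitment then builds a forecast in steps:

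- "It is estimated that around 300 patients per practice (based on an average practice size) will undertake the pre-screening over a 12 month period".
- Over 40 practices this is "approximately a total of 12 000 patients completing the pre-screen survey".
- "Out of these 12 000, we expect dyspnoea rates of around 10" per cent.
- For variation in severity and duration of breathlessness, and for consent, "we are allowing for 3/4 patients not to proceed to the CDSS, resulting in a total of 400 (200 per arm".
- From this the section derives "a target for each practice to recruit a minimum of 10 participants".

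Statistical analyses reaches the same total by another route. It asks for 90% power to detect a four-point difference in D-12 at the 0.05 level, with SD 15, individual autocorrelation 0.65 and 40 practices. That requires nine participants per practice followed for 12 months. After a 10% drop-out allowance, "we aim to recruit 10 participants per cluster for a total of 400 participants".

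**The concern.** The forecast is presented as a calculation whose result is 400, but the inputs printed beside it give a smaller number. The fraction and the total cannot both be right.

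This matters because 400 is the number the primary comparison needs, and this paragraph is the article's only argument that 40 practices can supply it in 12 months. If the fraction is the slip, nothing in the design changes. If the total is the slip, the planned screening volume does not support the stated power. As written, a reader cannot tell which applies, or whether 7.5 recruits per practice would be on plan or a quarter short.

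**Working it through.** **1. The sample-size requirement (Statistical analyses), reproduced first.**

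Inputs from the article: difference 4, SD 15, autocorrelation 0.65, 20 practices per arm, m = 9 completers per practice, intra-cluster correlation (ICC) up to 0.10. Assumptions where the article is silent: two-sided test, baseline-adjusted comparison, practice effect fully stable over time, t reference distribution with 38 degrees of freedom.

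Variance of the treatment difference = 2 x SD² x [1 + (m − 1) x ICC] x (1 − r²) / (20 x m), with r = [m x ICC + (1 − ICC) x 0.65] / [1 + (m − 1) x ICC].

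At ICC = 0, r = 0.65 and 1 − r² = 0.5775:

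- m = 9: SE = √(450 x 0.5775 / 180) = 1.202; 4 / 1.202 = 3.33; power 0.900.
- Over ICC 0 to 0.10, power at m = 9 stays between 0.896 and 0.902.
- Drop-out: 9 / 0.9 = 10 per practice; 360 / 0.9 = 400.

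The stated 90% power, the robustness to ICC up to 0.10 and the total of 400 all reproduce.

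**2. The recruitment chain (Participant recruitment).**

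- 40 x 300 = 12 000 screened. This agrees with the article.
- 12 000 x 0.10 = 1200 with dyspnoea.
- 1200 x (1 − 3/4) = 300 consenting. The article states 400.
- 300 / 2 = 150 per arm (stated: 200); 300 / 40 = 7.5 per practice (stated: 10).
- Shortfall: 100 / 400 = 25%.

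**3. What would give 400, changing one input at a time.**

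- Share proceeding: 400 / 1200 = 1/3, so 2/3 not proceeding.
- Dyspnoea rate: 400 / (12 000 x 1/4) = 13.3%.
- Number screened: 400 / (0.10 x 1/4) = 16 000, or 400 per practice.

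**4. Whether another reading closes the gap.**

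- Drop-out: it applies after recruitment, and 300 / 0.9 is only 333.
- Consent: it is already named as a reason for the three quarters.
- Proceeding to the CDSS read as the intervention arm only: the result of the same sentence is split by arm, so the fraction covers both arms.

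**5. Power if 300 were the true yield (same formula and assumptions).**

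| Scenario | m per practice | SE (ICC 0) | Power (ICC 0) | Power range, ICC 0 to 0.10 |
|---|---|---|---|---|
| 400 recruited, 10% lost | 9 | 1.202 | 0.900 | 0.896–0.902 |
| 300 recruited, none lost | 7.5 | 1.316 | 0.842 | 0.839–0.846 |
| 300 recruited, 10% lost (270) | 6.75 | 1.387 | 0.802 | 0.800–0.809 |

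A normal approximation in place of t adds about two points to the last row (0.82 to 0.83). If the practice effect is not stable over time and the ICC is above zero, power is lower at both sizes. For example, with ICC 0.10 and a cluster autocorrelation of 0.8, it is 0.76 at m = 9 and 0.68 at m = 6.75.

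**The case against.** The strongest reply is that this paragraph is a forecast and not a design input. Its figures are hedged as estimates, no analysis or power figure is derived from it, and the commitment in both sections is 10 per practice. Since 1200 x 1/3 is exactly 400, the likeliest explanation may be a wrong fraction, and correcting it would leave every design number untouched. That largely stands, and it limits how serious the point is. It does not remove the point: hedged wording does not plausibly stretch 10% to 13.3%, and 40 x 300 = 12 000 is exact.

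The 80% figure can also be challenged because it counts only 12-month completers. The primary model uses the 3- and 6-month visits too, so participants lost late still contribute. This stands, and it is why the power consequence is given as 80% to 84%.

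Three stronger readings are tempting, and the documents do not support them:

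- **That the trial will miss its sample.** The article does not show which input is wrong, so the mismatch cannot establish this.
- **That power falls from 90% to the low or mid 70s.** An unconstrained comparison of changes gives about 72% to 77% at 6.75 completers per practice, but it gives only about 84% to 87% at nine. The part attributable to recruitment is about 11 points. The remainder is a separate question of estimator.
- **That a minimum of 10 per practice is an error because the screening figure is an average.** A floor set as a site target is ordinary practice, and Statistical analyses already treats 10 as the per-cluster number behind 400. Any estimate of how many practices would reach 10 needs a distribution that the article does not give.

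**Conclusion.** The stated total does not follow from the stated rates. They give 300 (150 per arm, 7.5 per practice) against 400 (200 per arm, 10 per practice), and nothing else in the article reconciles the two. This part is plain arithmetic and needs no assumption.

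The requirement of 400 is sound on its own inputs, so the fault lies in the recruitment forecast and not in the sample-size calculation. The fall in power to about 80–84% is conditional on 300 being the true yield. It also rests on a two-sided test, baseline adjustment, a stable practice effect and 38 degrees of freedom.

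This is a feasibility inconsistency that should be fixed. It is not a defect that invalidates the design, because correcting a single fraction may be all that is needed.

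**What to change.** Reconcile the chain in Participant recruitment in one of two ways:

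- **(a)** If the sponsor's working assumption is that one third proceed, state that two thirds do not. The 400 participants and 90% power then stand unchanged.
- **(b)** If three quarters is the real assumption, state the yield as 300 (150 per arm, 7.5 per practice) and restate power for four points as about 80–84%. Note that 400 would need about 16 000 screens, or 400 per practice.

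The cost is one paragraph of text. Under (b) there is also a less favourable yield and power figure, or a larger screening requirement, to declare. The sample-size inputs and the analysis model need no change on account of this point.

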### Procedures

All patients who book a GP consultation will receive an SMS prior to their appointment with a standard set of questions developed by BetterConsult that is completed on their smartphone. An additional mMRC question has been added to this to identify any patients with breathlessness. Patients who indicate an mMRC ≥1 will also be asked the timeframe of their breathlessness and to answer the Dyspnea-12 (D-12) questionnaire.^28^

Patients who have an mMRC ≥1 and have been experiencing breathlessness for ≥4 weeks will be invited to participate in the BREATHE study and will complete an e-consent on their smartphone. The e-consent is an ‘easy-read’ format designed to be read on a smart phone. All consented participants will be followed up at 3, 6 and 12 months, but their intervention will differ depending on which intervention arm their GP practice is randomised to:

#### Arm 1: pre-screening for dyspnoea and standard of care management (figure 2)

Figure 2: After obtaining consent, the participant will complete the Five-level EuroQol five-dimensional questionnaire (EQ-5D-5L)^29^ quality of life questionnaire and the Patient Health Questionnaire-4 (PHQ-4).^30^ At 3, 6 and 12 months from the date of consent, a follow-up SMS will be sent to participants to complete the mMRC, D-12, EQ-5D-5L and PHQ-4 to assess changes in breathlessness and quality of life. They will also be asked if they had any hospital admissions for the health economics evaluation. De-identified information on participant demographics, medical and smoking history, vital signs, referrals, radiological and pathology results, medications and new diagnoses will be automatically extracted directly from the GP eMR for the assessment of GP management on a regular basis during follow-up.

**Figure 2 F2:**
[figure not shown]
Study flowchart for Arm 1: pre-screening for dyspnoea and standard of care management. All participants at 3, 6 and 12 months will receive an SMS message to complete the following questionnaires: mMRC, D-12, EQ-5D-5L as well as have their Electronic Medical Records extracted monthly by Better Consult for the duration of the study. BREATHE, Breathlessness Rapid Evaluation And ThErapy; CDSS, clinical decision support system; GP, general practitioner; mMRC, modified Medical Research Council.

#### Arm 2: pre-screening for dyspnoea and BREATHE CDSS-guided management (figure 3)

Figure 3: After obtaining consent, the participant will complete additional questions about their breathlessness and the EQ-5D-5L and the PHQ-4. Responses to all questions will be forwarded to the GP for review prior to the consultation. The GP will be directed to use the BREATHE CDSS to enter more information about the participant such as vital signs and physical examination results. This information, along with the patient responses and information extracted from the eMR, will be used in the CDSS algorithm to provide probabilities for most likely diagnoses and the most relevant diagnostic tests to perform. It is expected that the GP will use this information to inform their management, but decisions will always be at the discretion of the GP. The GP will enter their provisional diagnosis into the CDSS and if they plan to refer the participant for diagnostic tests or to a specialist. For the following provisional diagnoses, the GP will ask participants to complete the disease-specific questionnaires:

COPD Assessment Test (CAT)^31^ for participants provisionally diagnosed with COPD.Chronic Airways Assessment Test (CAAT)^32^ for participants provisionally diagnosed with asthma.Kansas City Cardiomyopathy Questionnaire (KCCQ)^33^ for participants provisionally diagnosed with heart failure.Nijmegen Questionnaire^34^ for participants provisionally diagnosed with dysfunctional breathing.

**Figure 3 F3:**
[figure not shown]
Study flowchart for Arm 2: pre-screening for dyspnoea and BREATHE CDSS intervention. All participants at 3, 6 and 12 months will receive an SMS message to complete the following questionnaires: mMRC, D-12, EQ-5D-5L as well as have their Electronic Medical Records extracted monthly by Better Consult for the duration of the study. BREATHE, Breathlessness Rapid Evaluation And ThErapy; CDSS, clinical decision support system; GP, general practitioner; mMRC, modified Medical Research Council.

At all scheduled appointments from this point up until 12 months, the GP can access the CDSS to update results or information and the algorithm will recalculate the probabilities for diagnoses. At 3, 6 and 12 months, the participants will attend a clinic visit and the SMS sent prior to this appointment will include the mMRC, D-12, EQ-5D-5L and PHQ-4, relevant disease-specific questionnaire(s), and a questionnaire asking if they had any hospital admissions visits since their last visit. Also at 3, 6 and 12 months, the GPs will enter details of tests conducted and the outcomes and update their diagnoses. De-identified information on participant demographics, medical and smoking history, vital signs, referrals, radiological and pathology results, medications and new diagnoses will be automatically extracted directly from the eMR.

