### Data collection

All study data will be collected directly from the BetterConsult software of participant and GP entered information, as well as the medical information and results extracted directly from the eMR. All data will be de-identified using a 64-digit encrypted ID and uploaded into a highly secure cloud-based server housed by The George Institute for Global Health (TGI). This source data will be securely stored for 15 years. Only authorised trial staff from TGI will have access to the trial dataset. The Standard Protocol Items: Recommendations for Interventional Trials reporting guidelines were used for this protocol.^35^

All data are extracted directly from the participant, GP and practice databases and therefore considered source data, so no data monitoring is required to check for data transcription errors. There are no mandated tests or study procedures outlined in the protocol; therefore, compliance monitoring with respect to the protocol and missing data is also not required. To promote participant retention, the research team will stay in close contact with practice managers who will book the follow-up appointments for the consented patients. Data monitoring will identify upcoming and overdue visits to assist with this. Completion of the disease-specific questionnaires will also be monitored for sites randomised to the CDSS intervention arm, and if missing, the research team will contact the practice manager to follow this up with the participant.

There will be monitoring for any serious adverse events that could reasonably be considered related to study procedures. The intervention is intended solely to provide non-binding suggestions, which clinicians may choose to accept or disregard at their discretion. Therefore, clinicians retain full autonomy over all decisions regarding further investigations, management and diagnosis. The training of GPs and practice managers will cover the management of adverse events and will advise that any issues, problems or patient complaints be directed to the research team. Additionally, all participants (including practices, GPs and patients) are provided with full contact details for the relevant ethics committees in the participant information statements, should a serious adverse event or concern arise that could possibly be related to trial participation. Data monitoring for missed visits or missing data in the extraction will be conducted by the study team at TGI.

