### Economic evaluation

A within-trial cost-utility analysis will be conducted from a health system perspective to assess the cost-effectiveness of BREATHE CDSS over standard of care. Cost estimates will be based on all aspects of the intervention. Intervention costs associated with CDSS use will be determined from project financial records, including costs associated with ongoing technical support and maintenance of the CDSS. Hospitalisation costs and subsequent GP visits, referrals and tests, as reported at each follow-up visit, will be costed using Australian National Diagnosis Related Group cost weights and the Medicare Benefit Schedule (MBS), respectively. We will seek consent from all participants to access their MBS and Pharmaceutical Benefits Scheme data via Services Australia (EREC approval number RMS4167). The outcomes of interest will be differences in health-related quality of life measured using the EQ-5D-5L between CDSS and standard of care groups over a 12 month period.^39^ The latter will be converted into utility scores via published Australian value sets to determine the quality adjusted life year gain at 12 months. A joint modelling approach using multilevel modelling of both costs and effectiveness will be used to estimate the incremental cost per quality-adjusted life year gained and thus determine whether CDSS provides value for money. Finally, a budget impact analysis will be conducted to assess the fiscal impact on the Australian healthcare system with the potential implementation of the CDSS system at a nationwide level. A series of scenario analyses with varying different assumptions around costs, effects and the population of interest will be undertaken.

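### As written, the follow-up D-12 is triggered by date in Arm 1 and by a clinic visit in Arm 2, and other sections of the article contradict that difference

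*Protocol article*

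**What the plan says.** The Arm 1 section sets the trigger by calendar: "At 3, 6 and 12 months from the date of consent, a follow-up SMS will be sent to participants". It describes no appointment. The Arm 2 section, in the text after the Figure 3 caption, sets it by appointment for the same three time points: "the participants will attend a clinic visit and the SMS sent prior to this appointment will include the mMRC, D-12". The disease-specific questionnaires travel in the same Arm 2 message, and the GP enters tests, their outcomes and updated diagnoses at those times.

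Other places describe follow-up without that difference. Both figure captions state "All participants at 3, 6 and 12 months will receive an SMS message to complete the following questionnaires" and mention no visit. Procedures gives one set of times for everyone: "All consented participants will be followed up at 3, 6 and 12 months, but their intervention will differ".

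Data collection bases retention on contact with "practice managers who will book the follow-up appointments for the consented patients", and on tracking upcoming and overdue visits. Neither is limited to an arm. The same section says "There are no mandated tests or study procedures outlined in the protocol". Economic evaluation costs "subsequent GP visits, referrals and tests, as reported at each follow-up visit".

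**The concern.** The D-12 carries the primary outcome, participants report it themselves, and practices know their allocation. In such a trial the occasion for measurement should be the same in both arms. If one arm answers on a fixed date and the other answers ahead of an appointment, the interval since consent and the chance of answering at all can both depend on allocation.

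The planned analysis would not put this right. The mixed model described under Statistical analyses is indexed by nominal visit. Controlled multiple imputation tests how the result responds to different missing-data assumptions, but it cannot make the collection trigger equal.

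Two smaller matters follow from the same wording. The costing sentence refers to follow-up visits, which the article describes only for Arm 2. The three Arm 2 visits also sit badly with the statement that nothing is mandated, and Trial design does not list them as part of the CDSS arm. A reader cannot tell whether they are intervention or measurement. This affects whether their cost counts as a cost of the intervention.

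**Working it through.** **1. Passages side by side**

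| Place | Trigger for the follow-up D-12 | Visit described? | Limited to one arm? |
|---|---|---|---|
| Procedures | 3, 6, 12 months | No | No |
| Arm 1 section | SMS, counted from consent | No | Arm 1 |
| Arm 2 section | SMS before an appointment | Yes | Arm 2 |
| Captions, Figures 2 and 3 | SMS at 3, 6, 12 months | No | Same wording for both |
| Data collection | Booked appointments, overdue visits tracked | Yes | No |

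The Arm 1 and Arm 2 sections differ from each other. The captions agree with the Arm 1 pattern. The retention text, read literally, extends appointments to both arms. These cannot all describe one procedure.

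**2. The plan's own figure**

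Inputs from Statistical analyses: 40 practices, 9 analysed per practice (180 per arm), SD 15, difference 4, individual autocorrelation 0.65, ICC up to 0.10, significance level 0.05. Assumed because not stated: a two-sided test and a cluster autocorrelation of 1.

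- Variance of the contrast = 2 × 15² × D × (1 − r²) / 180, with D = 1 + 8ρ and r = [9ρ + (1 − ρ) × 0.65] / D.
- ρ = 0: D = 1, r = 0.65, D(1 − r²) = 0.578, power 91.5%.
- ρ = 0.05: D = 1.4, r = 0.7625, D(1 − r²) = 0.586, power 91.1%.
- ρ = 0.10: D = 1.8, r = 0.825, D(1 − r²) = 0.575, power 91.6%.

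With a t reference on 38 degrees of freedom these become 90.0%, 89.6% and 90.1%. Recruitment: 360 / (1 − 0.10) = 400. The stated 90% and 400 reproduce under these assumptions.

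**3. Loss of precision if completion differs by arm (assumed rates)**

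Starting from 10 recruited per practice, normal approximation, ICC 0.05 to 0.10:

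- 10% missing in both arms: 91.1% to 91.6%.
- 20% in Arm 1, 10% in Arm 2: 89.4% to 90.0%.
- 30% in Arm 1, 10% in Arm 2: 87.3% to 87.9%.

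Power falls little, so bias is the main risk.

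**4. Bias if completion differs by arm (assumed rates)**

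Let d₁ and d₂ be the proportions missing at 12 months, and g the difference in mean change between responders and non-responders, taken as equal in the two arms. In each arm the responder mean departs from the full-arm mean by d × g, so the contrast shifts by (d₁ − d₂) × g.

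| Gap d₁ − d₂ | g = 2 | g = 4 | g = 6 |
|---|---|---|---|
| 0.10 | 0.2 | 0.4 | 0.6 |
| 0.20 | 0.4 | 0.8 | 1.2 |

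The range of 0.2 to 1.2 points is 5% to 30% of the 4-point target (0.2/4, 1.2/4) and 7% to 42% of the 2.83-point minimum important difference (0.2/2.83, 1.2/2.83). This is a complete-case calculation. The 3- and 6-month scores in the mixed model may recover part of it. The sign depends on which arm loses more participants and on who is lost.

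**5. Timing**

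The article gives neither a D-12 time course nor an expected delay in visits, so no size can be put on a timing difference.

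**6. Resource use**

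The eMR extraction listed for both arms includes referrals, radiology and pathology results, medications and new diagnoses. MBS and PBS data are sought from all participants, subject to consent. GP visits are not in the eMR list, so they would rest mainly on MBS data. Both arms are asked about hospital admissions.

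**The case against.** The strongest reply is that one common procedure is intended and the article is loosely worded. Instrument, smartphone delivery and nominal times are the same in both arms, and the captions match. Windows, reminders and the rule for a missed visit are commonly left to the full protocol. The Arm 2 visits are plausibly part of CDSS-guided management, since the GP updates tests and diagnoses there. Controlled multiple imputation is planned for missing data.

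Most of this is fair, and it rules out three stronger readings that a reader might infer:

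- **An Arm 2 participant without a visit receives no D-12.** The Arm 2 text does not say the message goes out only if an appointment exists, and its caption promises one to all participants.
- **Arm 1 has no retention effort.** The booking and overdue-visit sentences are not restricted by arm. Where that section means CDSS sites alone, it says so, and there it concerns the disease-specific questionnaires.
- **Arm 1 records hospital admissions only, so costs compare a reported arm with an unreported one.** The eMR extraction and the MBS/PBS request cover both arms.

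The reply does not remove the conflict itself. If one procedure is intended, at least one of the two arm descriptions is wrong. If two are intended, measurement of the primary outcome depends on allocation. Omission of windows and reminders is not the complaint here; the article states two different triggers.

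**Conclusion.** The point holds as an inconsistency with a real risk attached, not as demonstrated differential collection. Followed as written, the Arm 1 and Arm 2 sections make the timing of an open-label, self-reported primary outcome depend on allocation, and possibly its completeness too. The 0.2 to 1.2 points rest wholly on assumed completion gaps and responder differences, and the direction is undetermined. The sample-size calculation is not in dispute here. The costing issue reduces to one phrase that does not fit the sources planned for both arms. The status of the Arm 2 visits needs a clear statement.

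**What to change.** 1. State one rule for both arms: the 3, 6 and 12 month D-12, mMRC, EQ-5D-5L and PHQ-4 go out by SMS on a date counted from consent, with the same window and the same reminders, whether or not an appointment exists. Align the two arm sections, the captions and the retention text to it.
2. In Economic evaluation, replace the reference to visit reports as the source for GP visits, referrals and tests with the eMR and MBS sources already planned for both arms.
3. Reconcile the Arm 2 clinic visits with the statement that no tests or procedures are mandated, and say whether those visits are part of the intervention being evaluated.

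The cost is a scheduling rule in the SMS software and some wording. The drawback is that Arm 2 GPs may see scores collected some days away from the visit. The change is best made before follow-up data accrue, because an unequal collection trigger cannot be repaired afterwards.
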